### Inclusion and exclusion criteria

The total sample of 40 healthy pregnant women will be recruited in the region of Wageningen and Nijmegen, The Netherlands. In order to be eligible to participate in this pilot trial, women must meet all of the following inclusion criteria:At least mild symptoms of depression or anxiety.Start daily probiotic/placebo product intake between 26 and 30 weeks gestational age and continue until delivery. The lower limit of ≥ 26 weeks and the upper limit of 30 weeks allow time to complete at least 8 weeks of probiotic intake prior to delivery. Gestational age is based on last menstrual period and the early ultrasound scan.

A potential participant who meets any of the following exclusion criteria will be excluded from participation in this pilot trial:Multiple pregnancy (increased obstetric risk).High suicidal risk according to suicidality subscale score on the MINI (see screening).Illegal drug use.History of psychoses and bipolar disorder.Inflammatory bowel disease (i.e. ulcerative colitis, Crohn’s disease).Other autoimmune disorders and/or treatment with immunosuppressive therapy.Known pre-existing diabetes mellitus, hyperemesis gravidarum, hypertensive disorders or liver or renal disease.Malignancy and/or treatment with radiation or chemotherapy.History of major gastro-intestinal surgery (e.g. colectomy).Hypersensitivity or allergy to any ingredients in the probiotic/placebo product.History of using oral multi-species probiotic Ecologic® Barrier.Presently using food containing probiotics (e.g. Actimel) and not willing to stop these at least 2 weeks prior to the start of the probiotic/placebo product intake.No mastery of the Dutch language.

### Sample size calculation

The main aim of the PIP pilot trial is to evaluate the feasibility and acceptability of a probiotic intervention in pregnant women suffering from depressive and/or anxiety symptoms. Since the pilot study will lay the basis for designing a larger RCT, the sample size calculations are based on a full RCT. An a priori power analysis to estimate the sample size was conducted using G*Power 3.1. An effect size of *f* = 0.187 was used for the sample size calculation, based on the prior studies of Benton (2007) [26] examining the effect of probiotics on symptoms of depression in healthy volunteers with elevated levels of depression. With a significance level of 5% and power of 80%, including 60 women per arm (total of 120) would be required to examine probiotic effectiveness in reducing depressive symptoms. To account for dropout, poor compliance, antibiotic use around the time of the intervention period and pregnancy complications, all of which may negate any potential effects from the probiotic/placebo product, we estimate that a total of 150 women would be needed for a full trial. Since the primary aim of the present pilot trial is to examine feasibility and acceptability, recruiting a total of 40 women (20 women per arm (~ 27% of a full trial)) would be adequate for this outcome. No interim analysis of preliminary results will be conducted given the expected relatively short duration of the pilot study and given that the study is labeled as minimal-risk research.

### Randomization, blinding and treatment allocation

The 40 women will be randomly allocated to either the probiotic arm or placebo arm. A computer random number algorithm (1:1 allocation ratio) at Winclove probiotics B.V. will randomize women, using blocks of 4. A staff member at Winclove Probiotics B.V., who is not involved in the study, will sequentially label probiotic boxes (including number sachets with the probiotic or placebo product). The staff member will also create a sealed randomization list and sealed code break envelopes per participant in order to keep the trial investigators unaware of the allocation sequence and randomization code, and to maintain blinding until the end of the pilot trial. The randomization code will not be released until the last participant has finished the pilot trial. The CI, who is unaware of participant assignment in the allocation sequence, will distribute the sequentially numbered probiotic boxes. Participants will be assigned to a numbered box upon order of providing informed consent. Next to investigators, the participants, care providers and outcome assessor are blinded to the participant’s allocation. The Principal Investigator (PI) has access to the randomization data in case it is necessary to unblind. The blind may be broken for a serious and unexpected event, if it is essential for the medical management of subjects, or may provide critical safety information about the intervention that could have implications for the ongoing conduct of this trial. Sealed code break envelopes per participant are accessible within 24 h. In the event of a code break, the name of the code breaker, the signature and the date and time will be recorded on the outside of the envelope.

### Intervention procedure

#### Probiotic/placebo formulations

Participating women will be randomly allocated to either control group (placebo) or intervention probiotic group (multispecies probiotic Ecologic® Barrier, Winclove Probiotics B.V.) once daily for 8–14 constituent weeks. The probiotic food supplement is a freeze-dried powder in sachets and contains 2,5 × 10^9^ CFU/g. One dose (one sachet) consists of a total of 5,0 × 10^9^ CFU (2 g). The recommended dosage of the probiotic product of one sachet per day is in concordance with probiotic dosages used in previous studies examining Ecologic® Barrier and other multispecies probiotic products. The number of bacteria in a dose ranges from 10^9^ to 10^10^ CFU/dose, which is the normal amount of bacteria for studies in healthy volunteers and pregnant women [27–29]. The probiotic product contains the following bacterial strains: *Bifidobacterium bifidum* W23, *Bifidobacterium lactis* W51, *Bifidobacterium lactis* W52, *Lactobacillus acidophilus* W37, *Lactobacillus brevis* W63, *Lactobacillus casei* W56, *Lactobacillus salivarius* W24, *Lactococcus lactis* W19 and *Lactococcus lactis* W58 (total cell count 2.5 × 10^9^/g). In addition to the bacteria, the probiotic product contains the carrier of the product: maize starch, maltodextrins, inulin and fructo-oligosaccharides (FOS).

Preclinical studies suggest that prebiotics, such as FOS and inulin, can exert antidepressant and anxiolytic effects [30, 31]. Therefore, in order to properly assess potential effects of bacteria on maternal mood, the placebo intervention includes the same carrier of maize starch, maltodextrins, inulin and FOS, but no bacteria. The placebo is indistinguishable from the probiotic sachets in color, taste and smell (Winclove Probiotics B.V., The Netherlands).

#### Intake procedure

Participants in the probiotic and placebo intervention groups are provided with 108 sachets (one for each day of the intervention, total of 3,5 months). The contents of the sachets need to be dissolved in 100 mL water, milk or yoghurt. The solution containing the probiotic/placebo is to be ingested orally, preferably on an empty stomach. The participant will be advised to take the probiotic/placebo 2–3 h after antibiotic ingestion if taking antibiotics. The sachets are stored at room temperature in their original package.

The full RCT will not investigate probiotics as a single treatment, but will explore their properties as a food supplement in addition to patients’ current treatments, if applicable. Hence, the use of any kind of co-medication, therapy (e.g. cognitive behavior therapy) or alternative therapy (e.g. yoga, mindfulness, tai chi, etc.) is allowed and will be reported accordingly. Participants are requested to discontinue any other probiotic (such as probiotic yoghurts) two weeks prior to the start of the intake of the probiotic/placebo product and to refrain from taking any other probiotics during the whole trial period.

### Measurements and outcomes

#### Primary outcome

The primary outcome will be assessed as follows: feasibility will be assessed in terms of (A) recruitment (quantitative and qualitative), (B) retention (quantitative) and acceptability will be assessed in terms of (C) compliance (quantitative) and (D) participants’ impressions and experiences during the pilot trial (quantitative).

The primary outcome of a full RCT would include effectiveness of the probiotic, compared to placebo, in reducing anxiety and depressive symptoms during pregnancy. For that reason, key outcome measures of this pilot study will inform whether or not to proceed with a full trial after this study, and if so, the revisions that should be made to the study protocol before conducting a full RCT. These outcomes include (B) retention rate, (C) compliance (i.e. proportion of participants taking ≥ 80% probiotic/placebo and proportion of participants filling in electronic questionnaires at all time points) and (D) participants’ experiences of participation and perspectives on joining this and future probiotic trials. Table 1 shows the outcomes, progression criteria (where applicable), key outcome measures and time points for each outcome of this pilot study.

**Table 1 Tab1:** Primary outcomes, (key) outcome measures, time points for each outcome and progression criteria for a full RCT

Primary quantitative outcomes	Outcome measure and time point for each outcome	Progression criteria for full RCT^a^
A) Recruitment	1) The proportion of contacted participants scoring above the threshold for anxiety or depressive symptoms and who accept the invitation to participate in the pilot trial throughout the study	30 participants recruited in 6 months
	2) The number of participants recruited at each site	No criteria set
B) Retention rate	2) The proportion of participants completing the study from enrolment (t0) to follow up (t4)*	≥ 90% of enrolled participants^b^
C) Compliance	3) The proportion of participants taking ≥ 80% probiotic/placebo product between t0 and t1*	90% of participants^c^
	4) The proportion of participants filling in electronic questionnaires at all time points (t0, t1 and t4)*	90% of participants
	5) The proportion of participants filling in the cry diary at t4	90% of participants
	6) The proportion of participants filling in evaluation form at t4	90% of participants
	7) The proportion of participants collecting all maternal vaginal and microbial samples at t0 and t1	90% of participants^d^
	8) The proportion of participants collecting all infant microbial samples at t0 and t1	90% of participants
	9) The proportion of participants allowing collection of hair samples at t4	90% of participants
D) Participants’ impressions and experiences	1) Experiences and level of acceptability of electronic questionnaires and collection of biological samples	No criteria set
	2) Level of satisfaction (positive/negative aspect)	No criteria set
	3) Level of satisfaction (execution and organization)	No criteria set
	4) Level of acceptability of the trial in practice (perceived burden)*	Mean score of ≤3
	5) Level of acceptability of the trial in principle (future participation)*	Mean score of ≥8
Primary qualitative outcomes		
A) Recruitment	1) Participants’ moment of decision to join the pilot trial	No criteria set
	2) Reasons for participation	No criteria set
	3) Reasons for non-participation	No criteria set

^a^In case one or more progression criteria are not met, revisions to the study protocol should be considered prior to conducting the full randomized controlled trial (RCT)

^b^A rate > 90% is comparable to previous RCTs in pregnant women with depressive and anxiety symptoms [32, 33]

^c^A rate of intake ≥ 80% is similar to other (pilot) RCTs with probiotics and food supplements in pregnant and non-pregnant individuals [34, 35]

^d^The rates of adherence to vaginal and fecal sampling and hair-sampling protocols do not include unforeseen errors, for example, loss of biological samples due to storage problems, etc

*Key progression criteria

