**Fig. 1 Fig1:**
[figure not shown]
Standard Protocol Items: Recommendations for Interventional Trials (SPIRIT) figure displaying the pilot trial design and the outcome measurements. After screening for eligibility (t-1), women sign the informed consent form and complete the baseline questionnaire (t0). Participants are then randomized in the probiotic or placebo arm and receive either the probiotic food supplement or placebo. After randomization, filling in the baseline questionnaire and collecting maternal vaginal and stool samples, women start using either the probiotic food supplement or placebo. Measurements take place at 26–30 weeks of pregnancy (baseline(t0); 34–38 weeks of pregnancy (t1); 7 days after birth (t3), and 1 month after birth (t4)).

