#### Infant intestinal microbiota

Parents will collect two infant fecal samples at home on weeks 1 and 4 using similar collection methods to those applied in our previous studies [36, 38], to measure the relative abundance of infant intestinal bacteria. Samples will be immediately stored by the participants at − 20 °C, collected by investigators at t3 and taken back to the University for storage at − 80 °C. The microbial composition of the stool samples will be analyzed using PCR sequencing methods.

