### Strategies to improve adherence to the intervention protocol

During the first home visit when the participants receive the probiotic/placebo product and sampling kits, the CI will provide face-to-face adherence reminder sessions. Similar adherence reminder sessions will be held by phone at t1 and t3, and face-to-face at t4. This will include:Explanation about the importance of adhering to study guidelines on the daily intake of the study product, electronic questionnaires and collection of vaginal and microbial sampling.Instructions about taking the probiotic/placebo product, including timing, preparation, storage, and what to do in the event of missing a dose.Reinforcement that the sachets contain either probiotics or placebo.Instructions about the purpose and use of vaginal swabs and microbial collection tubes, and temporary storage of vaginal and microbial specimens after collection. Instructions on paper will be provided at t0 (see Additional file 3D-E).Notification of the importance of contacting the CI if experiencing any problems related to intake of the probiotic/placebo product (e.g. symptoms, lost sachets), electronic questionnaires or the collection of vaginal and/or microbial samples.Reinforcement that, if there are any questions related to the study or problems occur during the intervention period, the CI (or in case of absence, another research member) can be contacted by phone or e-mail.

Within 2 days after the first home visit, the CI will contact the participant to ask whether there were any problems with the probiotic/placebo product or questionnaires, and to inform them about the time/date of collecting vaginal and stool samples. In case there are problems, simple strategies for enhancing adherence to study protocol will be discussed. The participant will also have the opportunity to ask the CI any remaining questions.

Participants will receive an electronic reminder at t1 to fill in questionnaires and to collect vaginal and microbial samples, again including the instructions about the use of vaginal swabs and microbial tubes and storage of specimens after collection. The CI will contact the participant 2 days after the first reminder, to request the time/date of collection of microbial and vaginal samples. In the case of problems, the CI will discuss with the participant simple strategies to enhance collection and/or filling in of questionnaires.

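### Table 1 ties the 90% criterion for infant stool samples to t0 and t1, which both precede birth; the document's own schedule points to t3 and t4

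*Protocol article*

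**What the plan says.** Table 1 of the protocol article lists the primary outcomes with their time points and progression criteria. Under C) Compliance, item 8 reads "The proportion of participants collecting all infant microbial samples at t0 and t1", and its criterion is "90% of participants". The row directly above, item 7, covers the mothers and uses the same time points: "The proportion of participants collecting all maternal vaginal and microbial samples at t0 and t1".

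The legend to Fig. 1 defines the time points: "Measurements take place at 26–30 weeks of pregnancy (baseline(t0" for baseline, then "34–38 weeks of pregnancy (t1); 7 days after birth (t3), and 1 month after birth (t4". The legend to Fig. 2 repeats the definitions of t1, t3 and t4.

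The section on infant intestinal microbiota gives the sampling schedule: "Parents will collect two infant fecal samples at home on weeks 1 and 4". It then says the samples are "collected by investigators at t3 and taken back to the University". Table 2 analyses the infant fecal sample as the difference between t3 and t4.

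Footnote a to Table 1 says that when any criterion is missed, changes to the protocol should be weighed before the full trial. An asterisk marks the key criteria. Item 8 has none.

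**The concern.** Item 8 is one of the primary quantitative outcomes and carries a numerical threshold. The time point is part of its definition, since the Table 1 column is headed as giving both the measure and its timing. Both stated time points fall in pregnancy, so the row asks for infant stool before there is an infant.

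This leaves two unsatisfactory options at the end of the pilot. If the row is applied as printed, it fails whatever the women do, and footnote a is triggered by a labelling error rather than by poor adherence. If the team quietly scores t3 and t4 instead, the pilot reports a primary outcome against a criterion that differs from the published one. A correction recorded before analysis avoids both.

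A smaller inconsistency sits beside it. The infant samples are to be picked up by investigators at t3, on day 7, yet one of the two is not taken until week 4.

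**Working it through.** This is a cross-check of time-point labels. No sample-size or power formula is involved.

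**Inputs**
- Item 8 time points: t0 and t1 (Table 1).
- Item 8 threshold: 90% of participants (Table 1).
- t0: 26–30 weeks of pregnancy (Fig. 1 legend).
- t1: 34–38 weeks of pregnancy (Fig. 1 and Fig. 2 legends).
- t3: 7 days after birth; t4: 1 month after birth (same legends).
- Infant stool: two samples, in weeks 1 and 4 (Infant intestinal microbiota).
- Infant microbiota metric: t3 to t4 (Table 2).
- Planned sample: 40 women (Sample size calculation).

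**Step 1: number needed.** With all 40 women as the denominator, 0.90 × 40 = 36.

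**Step 2: number attainable as written.** Item 8 requires all infant samples at both t0 and t1. Every participant is still pregnant at t0, so the t0 sample cannot exist for anyone. The attainable count is 0 of 40, or 0%. A birth before t1 does not help, because the t0 sample would still be missing.

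**Step 3: number attainable at t3 and t4.** Week 1 corresponds to t3 and week 4 to t4. Both follow birth, so the proportion can lie anywhere from 0% to 100%, and the criterion is met when at least 36 of 40 women supply both samples.

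**Step 4: likely origin.** Items 7 and 8 carry the same time points. For item 7 they are right: maternal vaginal and fecal samples are taken at baseline and 8 weeks after the start of the intervention, and Table 2 analyses them from baseline to t1. The labels in item 8 were probably copied from that row.

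**Step 5: pick-up.** t3 is day 7. A sample taken in week 4 cannot be picked up then. The article does provide a home visit at t4, when leftover sachets are counted (Adherence assessment).

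**The case against.** The strongest reply is that the document already supplies the right schedule in two places, the infant microbiota section and Table 2. No one running the trial would score infant stool against a visit in mid-pregnancy, so the error touches a label and not the data collected. That largely stands. It limits the practical damage, but it does not make the printed criterion correct.

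The second reply is that item 8 has little weight. It has no asterisk. The text before Table 1 names the outcomes that inform whether to proceed as retention, product intake, completed questionnaires and participants' experiences; infant sampling is not among them. Footnote a asks only that revisions be considered. This stands in full. A reader might infer that the pilot's decision on a full trial hangs on an impossible target, and the document does not support that.

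Two stronger readings of the pick-up sentence also fail:
- A reader might infer that no pick-up can happen at t3 because that contact is by telephone: "Similar adherence reminder sessions will be held by phone at t1 and t3, and face-to-face at t4". That sentence concerns reminder sessions. The t1 session is by phone too, yet maternal samples may be handed over at t1 or t4, so a phone session does not exclude a pick-up at the same time point.
- A reader might infer that every week-4 sample would be lost. That is speculation: participants store samples at −20 °C, and the t4 home visit is still to come.

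What remains is that a week-4 sample is assigned a day-7 pick-up.

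**Conclusion.** The point holds as an internal inconsistency of time-point labels in a non-key progression criterion. As printed, item 8 can reach 0 of 40 against a required 36 of 40, and it would always trigger footnote a. The 36 assumes that all 40 planned women form the denominator; the 0 needs no assumption beyond the document's own definition of t0.

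A reader might take the 0% as a forecast of what the pilot will report. It is only what the literal wording yields; in practice t3 and t4 would very likely be used. The issue is a misstated prespecified criterion. It deserves correction because it belongs to a primary outcome with a numerical threshold, but it does not threaten the pilot or its main progression decision. The t3 pick-up of infant samples is a separate, smaller inconsistency.

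**What to change.** In Table 1, item 8, replace t0 and t1 with t3 and t4. Keep the threshold and denominator as they are, "90% of participants", in line with the neighbouring compliance rows. Nothing in the document calls for a different denominator here. Record the correction with a date before the compliance data are analysed, and check that the case report forms and spreadsheets carry the same labels.

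Separately, amend the pick-up sentence in the infant intestinal microbiota section so that it fits a week-4 sample, for example by naming the t4 home visit as the pick-up point.

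The cost is two wording changes, with no added procedure, visit or sample.

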#### Primary outcomes: quantitative

Recruitment: the CI will obtain data on the proportion of women agreeing to participate in the trial and the site of recruitment from the research database and Excel spreadsheet chart after completion of the pilot study and will report the data on Microsoft Excel spreadsheet charts (see “Study setting and recruitment”).Retention rate: dropouts and the reasons for withdrawal if known will be documented by the CI on case report forms (CRFs) throughout the pilot trial. New participants will not replace dropouts. Data on the proportion of women who complete the study will be collected from CRFs at the end of the study (see “Data management” and “Statistical analysis”).Compliance: the rates of adherence to probiotic/placebo intake, electronic questionnaires/evaluation form/cry diary and microbial, vaginal and hair samples will be recorded by the CI on CRFs and Microsoft Excel spreadsheet charts throughout the study (see also “Strategies to improve adherence to intervention protocol for information”).Participants’ impressions and experiences: participants will be requested by the CI to fill in a self-created evaluation form within 1 week after completion of the pilot trial at home. The questionnaire includes nine questions: five questions on how the woman experienced (1) filling in questionnaires during the pilot trial (i.e. length, number of questionnaires, electronic method), (2) collecting their own and infant stool samples and vaginal samples (i.e. number of samples, explanation about method of collection, potential difficulties in collecting samples) and (3) having hair samples collected. Four items measure level of satisfaction: two open-ended questions stating “Regarding the study in general, which aspects did you experience as most positive and negative?” and “Do you have any general remarks regarding execution and organization of this study?”. For the other two questions, participants rate the perceived burden of the trial on a scale of 0–10 (0 “no burden”, 10 “very large burden”) and likelihood of participating in a similar trial in the future (0 “no chance of future participation”, 10 “very high chance of future participation”).

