## Discussion and conclusion

Many expectant mothers experience symptoms of depression and anxiety during pregnancy, which can affect both the mother and the infant [1, 82, 83]. Most women remain untreated: only 14% of women with symptoms of prenatal depression or anxiety receive treatment [2].

There is a great need for accessible and effective (complementary) treatments that can be applied during pregnancy. There are indications that probiotics ingested during and after pregnancy can reduce symptoms of depression and anxiety postpartum [14]. Probiotics ingested by the mother may thus offer a promising and user-friendly intervention to complement current existing effective treatments aimed at reducing symptoms of anxiety or depression during pregnancy. The present study is the first study to investigate the feasibility and acceptability of a probiotic trial to reduce symptoms of maternal prenatal depression or anxiety in pregnant women. Results of this pilot trial will help make an informed decision whether or not to proceed with a full trial after the pilot trial, and if so, whether revisions should be made to the study protocol and procedures before conducting a full RCT.

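### Table 1 ties no result to not proceeding, and the two key acceptability means leave out women who withdraw

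*Protocol article*

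**What the plan says.** The Primary outcome section gives the purpose: "key outcome measures of this pilot study will inform whether or not to proceed with a full trial after this study", and, if the answer is yes, which revisions are needed. The abstract's discussion says the same of the pilot's results, and the Discussion and conclusion section speaks of an "informed decision whether or not to proceed with a full trial after the pilot trial".

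Table 1 stars five criteria as key: retention (at least 90% of those enrolled), product intake (90% of women taking at least 80%), electronic questionnaires at all time points (90%), and the two acceptability scores D4 and D5. D4 is "Level of acceptability of the trial in practice (perceived burden"), with the criterion "Mean score of ≤3". D5 is "Level of acceptability of the trial in principle (future participation"), with a mean of at least 8. Footnote a gives the consequence of a miss, for starred and unstarred criteria alike: "In case one or more progression criteria are not met, revisions to the study protocol should be considered", with the full RCT to follow.

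The section Primary outcomes: quantitative describes the source of D4 and D5: "participants will be requested by the CI to fill in a self-created evaluation form within 1 week after completion of the pilot trial". Table 1 places the form at t4. The same section says that dropouts are not replaced and that reasons for withdrawal are documented if known. No rating at withdrawal is described.

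**The concern.** There are two separate weaknesses in the rules that serve the pilot's main aim.

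First, the stated purpose and the stated rule do not match. The text says the results bear on whether a full trial goes ahead. The footnote speaks only of what to consider before that trial and does not separate a near miss on a minor item from failure of every key item. A reader of the final report could not tell from Table 1 which result would have counted against proceeding.

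Second, D4 and D5 measure how burdensome the trial is and whether a woman would join again. A woman who left because of the burden is among the best placed to answer, and she is not asked. If such women would rate the trial worse than those who finish, the means look better than the experience of the women randomised, and a criterion could be met that would otherwise be missed.

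**Working it through.** **Step 1. Read the decision rule.** Five starred criteria, each met or missed, give 2^5 = 32 patterns. Footnote a sends every pattern with at least one miss (31 of them) to the same place: consider revisions. None is tied to not proceeding. The size of a miss plays no part.

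**Step 2. Effect of leaving dropouts out of D4 and D5.**

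Inputs from the article: 40 women (Sample size calculation); retention passes at 90%, that is 0.90 × 40 = 36 completers (Table 1); thresholds 3 and 8 (Table 1); scales 0–10 (Primary outcomes: quantitative). The article gives no score for dropouts, so a range is assumed.

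All-women mean = (36 × completer mean + 4 × dropout score) / 40, with completers exactly at threshold:

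| Item | Assumed dropout score | Calculation | All-women mean |
|---|---|---|---|
| Burden (pass ≤ 3) | 5 | (108 + 20)/40 | 3.2 |
| Burden | 8 | (108 + 32)/40 | 3.5 |
| Burden | 10 | (108 + 40)/40 | 3.7 |
| Future participation (pass ≥ 8) | 5 | (288 + 20)/40 | 7.7 |
| Future participation | 2 | (288 + 8)/40 | 7.4 |
| Future participation | 0 | (288 + 0)/40 | 7.2 |

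Every row fails over all women while the completer mean passes. With 2 dropouts the worst cases are (38 × 3 + 2 × 10)/40 = 3.35 and (38 × 8 + 0)/40 = 7.6. With none there is no shift.

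**Step 3. How close to threshold must completers be?** With 4 dropouts at the worst score, the burden verdict flips if completers average above (120 − 40)/36 = 2.22 and up to 3.0. The future-participation verdict flips if they average from 8.0 to below 320/36 = 8.89. With milder scores the window narrows: a dropout burden of 5 flips the verdict only above (120 − 20)/36 = 2.78, and a dropout future-participation score of 5 only below (320 − 20)/36 = 8.33.

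**Step 4. How far retention guards against this.** The chance of reaching at least 36 of 40 is 0.63 if true retention is 90%, 0.26 at 85%, 0.08 at 80% and 0.02 at 75%. Heavy loss would therefore usually show up as a missed retention criterion.

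**Step 5. What a level counting against proceeding could look like.** For a 90% criterion, exact (Clopper–Pearson) 95% intervals are 76.3% to 97.2% at 36/40, 64.4% to 90.9% at 32/40 and 61.5% to 89.2% at 31/40. So 31/40 is the largest count whose interval excludes 90%. A result of 31 or fewer has probability 1.5% at a true rate of 90%, 41% at 80% and 70% at 75%.

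**The case against.** A reader might infer from footnote a that the pilot is unable to return a negative answer. The article does not support that. The Primary outcome section keeps the negative decision open, and the Discussion, under Infant microbiota and crying, makes a large trial conditional on feasibility and acceptability being shown, together with preliminary signs of effectiveness. Each criterion can be missed and reported as missed. What is absent is a stated rule, not the possibility.

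A reader might also infer that the scoring of D4 and D5 tilts the decision towards a full trial. That goes too far as well. The direction depends on dropouts rating the trial worse than completers, which is plausible but not shown; a woman lost for obstetric reasons need not do so. Dropouts are not ignored either: retention is its own key criterion with enrolled women as denominator, and form completion has a separate 90% criterion. Women may decline single assessments and stay in follow-up (Plans to promote participant retention and complete follow up), so a woman who finds one assessment too much can still give her rating. And since footnote a leads only to revision, the scoring today affects whether the design goes forward unchanged or is revised.

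Finally, the bare 90% cuts do not favour going ahead. A procedure with a true rate of 90% misses 36/40 with probability 1 − 0.63 = 0.37, which pushes towards revision.

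All of this stands, and it limits the point. It does not remove the mismatch between purpose and rule, or the missing ratings.

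**Conclusion.** The point holds in a limited form. Table 1 links no result, however poor, to not proceeding, although the article says in three places that the pilot informs that decision. This follows from the text and needs no assumption.

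D4 and D5 omit women who withdraw. While retention passes, dropouts can hide a shift of at most 0.7 points in mean burden and 0.8 points in mean future participation when completers sit exactly at threshold. Form non-response among completers could add to this. The shift is enough to reverse either verdict, but only if completers average near the threshold and dropouts would have scored clearly worse. The dropout scores are assumed, and the direction is an expectation rather than a finding.

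Safety is not affected. The point bears on how clearly the pilot can answer its own main question.

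**What to change.** 1. Offer the two 0–10 items at withdrawal, as an option, alongside the recording of reasons.
2. Judge D4 and D5 over all randomised women. Report the number who answered and a sensitivity range for those who did not, for example with the scale ends as the outer bounds.
3. Amend footnote a to state, for the starred criteria, which level of failure counts against proceeding. For the three 90% criteria one option is a result whose exact 95% interval excludes 90% (31/40 or fewer); the two means need a level of their own. The cut-offs are the sponsor's choice. Report exact intervals for the proportions.

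The cost is small: new wording in Table 1 and two optional questions. The scores may look slightly less favourable. According to Trial status, 35 women had consented and 18 had completed at submission, so ratings from women who withdrew before the change may be missed. The Amendments section requires ethics committee approval for changes that may affect conduct, so an amendment may be needed. Where that is no longer practical, the denominator and the sensitivity range can still be reported at analysis.
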